#### Intervention component details

Components of the intervention can be found in Table 2.

**Table 2 T2:** Intervention components

**Intervention component**	**Purpose**
Registered Dietitian Consultations	Provides personalized nutrition education and behaviour modification strategies related to dietary intake
Exercise Physiologist Consultations	Provides physical activity education and behaviour modification strategies related to physical activity
Personalized step goal and physical activity tips	Provides motivation to increase physical activity
Daily wear of pedometer	Provides opportunity for self-management and bio-feedback
Nutrition education videos	Provides nutrition education for self-management
Log book	Provides opportunity for self-management
Coffee Talk	Provides social context and peer support

#### Nutrition counseling and education component

During Baseline Visit 2, each participant will meet with a Registered Dietitian for an initial nutrition counseling session of approximately 1 hour. This session will involve a review of the baseline 3 day food record, suggestions targeting reduced energy intake, and counseling on behaviour change strategies including goal setting, self-monitoring, stimulus control, and social support [57]. Each participant will be provided with methods for 454 a daily caloric reduction of 500–750 kcal. Each week, participants will log on to the intervention website to access new nutrition education sessions directed at supporting improved nutrition behaviors, weight loss, and behaviour change.

#### Physical activity counseling session and promotion component

During Baseline Visit 2, participants will meet with an exercise specialist to discuss goals, barriers to physical activity, personal strategies for increasing activity, and walkability of the participant’s neighbourhood. They will discuss the results of their VO_2_ test in relation to goal setting. Each participant will then receive a pedometer and a personalized daily step goal for Week 1. Participants will wear the pedometer daily, during the waking hours. Each subsequent week, participants will log on to the intervention website to receive a new individualized daily step goal. Participants will be instructed to attempt to meet the step goal in whatever way they feel capable, and will be provided with new 'tips’ each week. This method is thought to be well suited to LSS patients, as opposed to traditional time or distance goals for walking, given that participants can accumulate steps in small bouts throughout the day and within their homes. The goal will be to increase steps per day by a total of 20% by the end of the 12 week intervention period. The goal will be calculated as an increase of 1.3% above baseline for weeks 1–6 and 2% for weeks 7–12.

#### Intervention website training

During Baseline Visit 2, each participant will be guided through the login process for the intervention website, as well as instructed regarding how to navigate the website. During the initial registration, participants will enter their baseline daily step count, as determined from the 7-day activity monitoring. This value will be used to calculate the personalized weekly step goals.

#### Log book training

During Baseline Visit 2, each participant will be instructed regarding how to fill out the daily log book. Over the 12 week intervention period participants will record the following daily: food and water intake, physical activity: daily steps as well as duration (minutes) and intensity (mild, moderate or severe) of any structured activity, sleep (hours), mood, and medications.

#### 12- Week Intervention (at participants’ home)

Starting the day of Baseline Visit 2, each week for 12 weeks participants will log on to the e-health intervention website to access weekly inspirational quotes, their personal weekly physical activity goal (steps) and tips regarding how to achieve this goal. Each week they will also access a nutrition education video. The nutrition video topics are as follows: Weight loss – secrets to success; Meal timing and tracking; The art of snacking; Environment for success; Food diaries; Feeling full with fibre and hydration; Be a fat and calorie detective; Saboteurs to weight loss parts 1 and 2; Energy density; Mindful eating; and The 10 habits of successful weight loss maintainers. Every three weeks there will be an optional 'Coffee Talk’ meeting. These meetings will be casual gatherings meant to provide social context and support to participants. A member of the study staff will be present at each Coffee Talk to discuss progress and ideas. These meetings will be announced through the intervention website. At any time, participants will be able to access content from previous weeks via the archives.

#### 6-Week check-in session

The 6-week Check-in session will be at mid-intervention. Participants will meet with the Registered Dietitian and Exercise Physiologist for a second time to discuss individual progress, barriers to success and suggested modifications.

#### Follow-up

There will be two follow-up testing time points. The first will be directly following the intervention at 13 weeks and the second at 24-weeks. Protocols for follow-up testing will be identical to baseline testing with two visits at each time point. Each follow-up will include a visit to the University of Calgary Human Performance Lab as well as a visit to Mount Royal University Exercise Sciences Lab. At the Human Performance Lab participants will have DXA testing, anthropometric measurements, a blood draw, and instructions regarding how to complete the final 7-day activity monitoring and 3 day food record. At the Exercise Sciences Lab, participants will complete the follow-up questionnaire, Self-Paced Walking Test, balance testing, neurological impairment score and VO_2_ peak testing. The questionnaire will be identical to the baseline questionnaire, with the addition of the change questions. The change questions are on 7-point likert scales and assess perceived change in activity level, mood, overall health, calorie intake, vegetable intake and fibre intake.

All participants will be invited back one month after each follow-up testing session to review their results with study personnel. Those assigned to the control group will be offered the opportunity to try the intervention once the study is complete.

### Magnetic resonance imaging

Following the 12-week intervention period for each participant, we will access the clinical magnetic resonance imaging (MRI) report. The variables to be extracted from the MRIs include dural cross sectional area at each lumbar level, as well as cross-sectional area of the paraspinal muscles (psoas and multifidus).

### Sample size estimate

Pilot study data was used to power the planned RCT. The pilot study provided an estimate of the variability in the number of steps taken for 10 participants with LSS. We used a crude estimate of the sample standard deviation for steps in place of the unknown population standard deviation. Our main study outcome is number of steps at the end of the 12-week intervention. For the pilot study, an average increase of 375 steps was encouraged during each six-week period. At the end of the study, an average increase of 750 steps was anticipated. This was used to judge whether the intervention was effective. With α = 0.05 and a mean difference of 750 steps at the end of study, the standard deviation of the difference was calculated as follows:

$$\mathrm{Std}.\mathrm{Dev}\;\mathrm{of}\;\mathrm{diff}=\tilde{\sigma }=\frac{\left(L-S\right)}{4}=\frac{\left(5000-0\right)}{4}=1250$$

L equals largest and S equals smallest anticipated difference in the number of steps from baseline to follow-up period.

The formula for the sample size required, per group, (with α = 0.05, the probability of type I error, 80% power and an effect size of 0.6) to compare two population means, *μ*_1_ and *μ*_2_ with common variance, *σ*^2^, is

$$n\;=\;\frac{2{\left(Z_{1-\alpha /2}+Z_{1-\beta }\right)}^{2}}{{\left(\frac{\mu_{1}-\mu_{2}}{\sigma }\right)}^{2}}=\;\frac{2{\left(1.96+0.84\right)}^{2}}{{\left(\frac{750}{1250}\right)}^{2}}=43.60\approx 44$$

We concluded that a sample size of 44 people per group would be needed to detect a between-group difference of number of steps taken from baseline to week twelve. Based on the dropout rate for the pilot, we anticipate a potential dropout rate of 20% for the RCT. We will therefore aim to recruit 106 participants (53 per group). This number has been deemed feasible based on the volume of lumbar spinal stenosis patients seen through the University of Calgary Spine Program (approximately 500 per year).

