### Blinding and randomization

After completing the screening process participants will be randomly assigned to either the intervention group (n = 53) or the control group (n = 53). A computer-generated randomization sequence produced using R statistical analysis program will be used. Participants will be allocated to the group by the Study Coordinator, and will be aware of the allocated group. Those assigned to the control group will be offered the opportunity to try the intervention once the study is complete. All study investigators including the statistician, and research staff collecting data will be blinded to group allocation (single blind design). Participants will be asked not to comment to assessors regarding allocation.

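### The SD of 1,250 steps comes from an anticipated range that excludes any decline and does not fit the plan's own mean changes, so the stated 80% power is unsupported

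*Protocol article*

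**What the plan says.** All the relevant text is in the protocol article, mostly under Sample size estimate.

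- **Source of the SD.** The section opens by saying that pilot data on 10 participants supplied an estimate of variability, and then: "We used a crude estimate of the sample standard deviation for steps in place of the unknown population standard deviation". No pilot SD is reported.
- **How the SD is obtained.** It is (L − S)/4 = (5000 − 0)/4 = 1,250, with the definition "L equals largest and S equals smallest anticipated difference in the number of steps from baseline to follow-up period".
- **Mean change.** "At the end of the study, an average increase of 750 steps was anticipated". The same 750 is then used as the difference between two population means with a common variance: "With α = 0.05 and a mean difference of 750 steps at the end of study".
- **Result.** The formula uses "the probability of type I error, 80% power and an effect size of 0.6" and gives 44 per group, described as the number "needed to detect a between-group difference of number of steps taken from baseline to week twelve".
- **Recruitment.** "we anticipate a potential dropout rate of 20% for the RCT", hence 106 recruits. Under Blinding and randomization, participants are "randomly assigned to either the intervention group (n = 53) or the control group (n = 53").

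**The concern.** Dividing a range by 4 is a rough rule for a fairly symmetric variable whose extremes lie about 2 SD either side of the mean. Applied to 0 and 5,000, it describes changes centred on +2,500 with almost nobody declining. The rest of the calculation assumes something else: a mean change of 750 in the intervention arm and, because the between-group difference equals that whole increase, a mean change of about 0 in controls. The section also presents the variability as pilot-based, while the number used comes from two anticipated extremes.

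This SD is the only variability input. The effect size of 0.6, the 44 per group, the 106 recruits and the 80% power all depend on it, and steps is what this section calls the main outcome. If the SD has no sound basis, neither has the claim that the trial is fully powered.

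**Working it through.** **Inputs.** Difference 750; SD 1,250 from S = 0 and L = 5,000; two-sided α 0.05 (z = 1.96); 80% power (z = 0.84); 1:1 allocation; 53 recruited per group; 20% dropout. All are from the protocol article.

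**1. Reproduce the plan's figure.** n = 2 × (1.96 + 0.84)² / (750/1250)² = 15.68 / 0.36 = 43.56, so 44 per group. Power at 44 per group is 80.4% by the normal approximation and 79.5% by the t-test. The plan's figure reproduces.

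**2. What range/4 implies.** The midpoint of 0 and 5,000 is 2,500, and 2,500 ± 2 × 1,250 gives exactly 0 and 5,000. The implied mean is 2,500/750 = 3.3 times the planned mean increase.

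**3. What SD 1,250 implies at the planned means, for normal changes.**
- Intervention arm, mean +750: P(change < 0) = Φ(−750/1250) = Φ(−0.6) = 27%.
- Control arm, mean 0 (inferred): P(change < 0) = Φ(0) = 50%.

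Both contradict a smallest anticipated change of 0.

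**4. Could a non-normal shape rescue the figure?** The largest SD possible on 0 to 5,000 with mean m is √(m × (5000 − m)).
- m = 750: √(750 × 4250) = 1,785. A skewed intervention arm could therefore have SD 1,250, although range/4 would not be the rule for such a shape.
- m = 0: the largest SD is 0. A control arm with mean 0 and minimum 0 cannot share a common SD of 1,250.

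**5. Sensitivity of power to the SD.** The documents give no alternative SD, so these values are assumptions. The difference is held at 750; n is 15.68/(750/SD)², rounded up. The 42 per group is 53 × 0.8 = 42.4, rounded down.

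| Assumed SD | Where it comes from | 750/SD | n per group for 80% | t-test power, 44 per group | t-test power, 42 per group |
|---|---|---|---|---|---|
| 1,000 | smaller value, for illustration | 0.75 | 28 | 94% | 92% |
| 1,250 | plan, 0 to 5,000 | 0.60 | 44 | 80% (79.5%) | 78% |
| 1,500 | −1,000 to 5,000, over 4 | 0.50 | 63 | 64% | 62% |
| 2,125 | −3,500 to 5,000, over 4 (symmetric about 750) | 0.35 | 126 | 37% | 36% |
| 2,500 | −5,000 to 5,000, over 4 (symmetric about 0) | 0.30 | 175 | 29% (28.5%) | 27% |

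**6. Precision of an SD from 10 people.** With 9 degrees of freedom and normal changes, the 95% limits are √(9/χ²) at the upper and lower 2.5% points, or 0.69 to 1.83 times the estimate.

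**The case against.** The strongest reply is that nothing has been miscalculated. 5000/4 is 1,250, and 750 with 1,250 gives 44 per group. That is correct, and the point concerns the input alone.

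Other parts of the defence also stand:
- L = 5,000 does not conflict with SD 1,250: (5000 − 750)/1250 = 3.4 SD above the planned mean, a reasonable extreme. The difficulty lies with S = 0.
- A skewed intervention arm on 0 to 5,000 with mean 750 could have an SD of 1,250.
- The control mean of 0 is inferred from the between-group difference equalling the whole anticipated increase. The article does not state it, nor does it say that the range describes controls.
- The authors call the estimate crude, and the pilot results are reported elsewhere. But admitting imprecision does not reconcile the range with the means.

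Stronger readings are tempting but not supported:
- *The trial is underpowered.* A reader might infer this from the larger SDs in the table. The true SD is not given and could be below 1,250, in which case power would exceed 80%.
- *The divisor should suit the range of 10 observations, giving a larger SD.* This would need 0 to 5,000 to be the observed pilot range; the article calls it anticipated.
- *The 750 is too optimistic because it assumes every step goal is met.* The article says the 750 was the yardstick for judging effectiveness, so it can be read as the difference worth detecting. That is a legitimate choice.

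**Conclusion.** The point holds as a defect in a planning input. The range used to derive the SD excludes declines, centres on +2,500, and cannot be squared with a mean increase of 750 together with a common variance in a control arm whose mean change is about 0. The stated source, pilot variability, is not what the formula uses. The 80% power is therefore unsupported.

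The size of any error is unknown. Over the assumed SDs of 1,000 to 2,500, power at 44 per group runs from about 94% to about 29%. This rests on a control mean change near 0, roughly normal changes for the percentages declining, and a simple two-group t-test on change; the planned mixed model may give somewhat different precision.

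**What to change.** Under Sample size estimate, replace the range/4 figure with the SD of the 12-week change in steps/day computed from the 10 pilot participants. Phase 2, intervention pilot reports accelerometry results, so the data should be in hand. Alongside it:

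- give the 95% limits of that SD (about 0.69 to 1.83 times the estimate; wider if fewer than 10 have both measurements);
- restate the power for a difference of 750 with 53 recruited per group after the anticipated dropout (about 42 per group), at the estimate and at both limits;
- state the control-arm mean change being assumed, and that an SD from pilot participants who all received the intervention is being applied to both arms.

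No outcome, analysis or recruitment target has to change. The cost is a short recalculation and a stated power that may be less favourable than 80%.

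### Minor arithmetic error in the dropout allowance: at the stated 20% dropout, 53 per group leaves about 42, not the required 44, and power is about 79% rather than 80%

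*Protocol article*

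**What the plan says.** All the inputs are in the protocol article under Sample size estimate. The calculation compares two means "with α = 0.05, the probability of type I error, 80% power and an effect size of 0.6". The effect size is "a mean difference of 750 steps at the end of study" divided by an SD of 1250, which is itself a quarter of an anticipated range of 0 to 5000 steps. The result is stated as a requirement: "We concluded that a sample size of 44 people per group would be needed".

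The dropout allowance follows directly, with the rate attributed to the pilot: "we anticipate a potential dropout rate of 20% for the RCT. We will therefore aim to recruit 106 participants (53 per group".

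The section Blinding and randomization fixes the same sizes, "the intervention group (n = 53) or the control group (n = 53", and the Abstract gives the total of 106. No formula is shown for getting from 44 to 53.

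**The concern.** A dropout allowance exists to leave the required number of evaluable participants after the expected losses. Here the required number, the expected loss and the recruitment target are all stated close together, and they cannot all hold. Either the trial recruits too few to keep 44 per group at 20% dropout, or the allowance is really for a lower dropout rate than the one stated.

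What is at stake is the accuracy of the headline sample size and of the 80% power claim attached to it, in a trial that the section Phase 3 describes as fully powered. An analysis plan could not reconcile the three numbers, and condensing a protocol into an article does not account for the mismatch.

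**Working it through.** **Inputs** (all from Sample size estimate): two-sided alpha 0.05 (z = 1.96), power 80% (z = 0.84), difference 750 steps, SD 1250 steps, dropout 20%, target 53 per group.

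**1. Reproduce the base figure.**
n = 2(1.96 + 0.84)² / (750/1250)² = 2 × 7.84 / 0.36 = 43.56, rounded up to 44 per group. This agrees with the document.

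**2. Reproduce the target.**
- Multiplying by 1 + 0.20: 44 × 1.2 = 52.8, rounded up to 53 per group, 106 in total. This matches the document exactly.
- Dividing by 1 − 0.20: 44 / 0.80 = 55 per group, 110 in total. This does not match.
- Rounding does not explain the gap: from the unrounded base, 43.56 / 0.80 = 54.4, which again rounds up to 55.

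**3. What 53 per group leaves.**
- 53 × 0.80 = 42.4 per group; 106 × 0.80 = 84.8 in total.
- Required: 44 per group, 88 in total. The shortfall is 1.6 per group, 3.2 in total.
- Largest dropout that still leaves 44: 1 − 44/53 = 0.170, or 17.0%.

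**4. Power by the document's normal formula.**
Power = Φ(0.6 × √(n/2) − 1.96).

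| Completers per group | 0.6 × √(n/2) | Power |
|---|---|---|
| 44 | 2.814 | 80.4% |
| 42.4 | 2.763 | 78.9% |
| 42 | 2.750 | 78.5% |

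Against the nominal 80%, the shortfall is 1.1 to 1.5 percentage points.

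**5. Difference detectable at 80% power.**
Difference = (1.960 + 0.8416) × 1250 × √(2/n).
- n = 44: about 747 steps.
- n = 42.4: about 761 steps.
- n = 42: about 764 steps.

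The design difference is 750 steps.

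**The case against.** The strongest objection is that nothing of substance turns on this. The loss is a little over one power point, and the inputs are much softer than that. The document calls its SD crude and takes it as a quarter of a guessed range. With 42.4 per group, assumed SDs of 1200 and 1300 would give about 82% and 76% power, so a 4% error in the SD moves power by about 3 points, more than the dropout slip does. This stands, and it limits the weight of the point. It does not make the stated figures consistent.

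A second objection is that the shortfall may never occur at the powered time point. The 20% is described as potential and is stated for the RCT, which runs to week 24, whereas the calculation concerns change to week twelve. The mixed-effects models named under Statistical analysis could use week 13 data from people lost later. This stands in part: about 42 per group at the end of the intervention follows only if the 20% applies at that point. But the sample size text takes no credit for partial data or for later losses, and it uses 20% as its working rate.

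A third objection is that the multiplication by 1.2 is an inference. That is correct. The mismatch between 44, 20% and 53 does not depend on how the 53 was reached.

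A reader might also go further and say that a two-sample t test needs 45 per group, that power is 77.6%, and that the detectable difference is 773 steps (t test figures at 42 per group). The document does not support using these as the size of the error. It plans with the normal formula and will analyse with linear mixed-effects models, so the t test is not its benchmark. By that test 44 per group already has only 79.5% power, so part of the apparent gap comes from the change of method and not from dropout.

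**Conclusion.** The error is real and minor. On the plan's own assumptions, 106 recruited with 20% dropout leaves about 42 per group, not 44. Power for 750 steps is then about 79% (78.5% at 42 per group, 78.9% at 42.4), not the stated 80%, and the difference detectable at 80% power is about 761 to 764 steps.

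This rests on the stated difference of 750, SD of 1250, two-sided alpha of 0.05 and normal formula, and on the 20% loss applying equally in both groups at the powered time point.

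A reader might infer that the trial is seriously underpowered or that its size invalidates the design. The figures do not support that: 1.6 completers per group and 1.1 to 1.5 power points would not change any conclusion about the trial's feasibility or design.

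**What to change.** The simplest change is to correct the sentence under Sample size estimate so that it says 106 recruited, with 20% dropout, leaves about 42 per group and about 79% power for a difference of 750 steps. This costs one sentence and changes nothing in the conduct of the trial.

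A variant is to state that 53 per group allows for 17% dropout. The text would then need to explain why 17% is used when the pilot led to an expectation of 20%.

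If the sponsor prefers to keep 44 completers per group at 20% dropout, the consistent target is 55 per group, 110 in total. That is four more participants, against about 500 patients a year that the document says are seen through the recruiting spine program. The Abstract and Blinding and randomization should then be changed to match. In either case, printing the inflation formula beside the result would let a reader check it.

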### Statistical analysis

Using the raw quantitative data from the participants of both groups we will present descriptive statistics summarizing the mean and standard deviation with respect to all the primary study variables. Age and sex distributions of the participants will be tabulated. Our goal is to establish reliable point estimates of the study variables and to characterize the variability within the two groups.

The independent variable will be the intervention, while the dependent variables will include steps/day, fat mass (%) and health related quality of life (SF-36 overall score). Linear mixed-effects models will be used to determine whether the changes for each time period (baseline to 13 weeks, baseline to 24 weeks) were significantly different between intervention and control groups. Repeated measures analysis of variance (RANOVA) will be used to examine within group changes from baseline to 13 weeks and from baseline to 24 weeks.

We will also examine changes in the following variables: Biochemical markers of obesity and associated co-morbidities including Plasma glucose, Serum adipokines (c-reactive protein (CRP), leptin, IL-1β, IL-6, IL-8, TNF-α, MCP-1 and insulin), and Serum lipids (total cholesterol, LDL cholesterol, HDL cholesterol and triglycerides); Physical function (Physical Function Scale of Swiss Spinal Stenosis Questionnaire); Walking capacity (Self-Paced Walking Test distance); Balance (mean deviation from centre of pressure from balance platform); Neurological impairment (Neurological Impairment Score); Pain (Symptom Severity Scale and visual analog scales); Back pain related disability (Oswestry Disability Index); Fear of movement (Tampa Scale for Kinesiophobia); Depression (CES-D total score); kilocalorie intake (kcal/day); Fat intake (grams/day); Vegetable and fruit intake (Canada Food Guide servings/day); Fibre intake (grams/day); and Change questions for activity, mood, overall health, calories, vegetable intake, and fibre intake. Clinical MRIs we will be used to assess whether imaging findings are predictive of change in the primary outcome variables following the intervention.

When an inferential test is performed, the level of significance, α will be set at 0.05, and results will be presented with p-values. In all tests, p-values less than 5% (< 0.05) will be considered statistically significant. All quantitative analyses and hypothesis will be performed using Minitab software, version 16 ^5^ and R programming language, version 2.15.1. Specifically, we will use the *gee* package, *pwr* package and *samplesize* package downloaded from the Comprehensive R Archive Network (CRAN) repository for our power and sample size calculations.

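### Comparing changes from baseline is valid but less precise than adjusting for baseline, and the within-arm ANOVA p-values say nothing about the intervention

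*Protocol article*

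**What the plan says.** The Statistical analysis section names the intervention as the independent variable, and steps per day, fat mass (%) and SF-36 overall score as the dependent variables. For the between-arm question, "Linear mixed-effects models will be used to determine whether the changes for each time period" (baseline to 13 weeks, baseline to 24 weeks) differ between intervention and control. A second analysis follows: "Repeated measures analysis of variance (RANOVA) will be used to examine within group changes" over the same two periods. Later in that section, "When an inferential test is performed, the level of significance, α will be set at 0.05", and any p-value below that level counts as significant. The within-arm analyses are therefore significance tests.

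The Sample size estimate section works on the change scale. It assumes "a mean difference of 750 steps at the end of study" and takes the SD from a range in which "L equals largest and S equals smallest anticipated difference in the number of steps from baseline to follow-up period". It concludes that "44 people per group would be needed to detect a between-group difference of number of steps taken from baseline to week twelve". No correlation between baseline and follow-up enters the calculation.

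**The concern.** Two things are at stake.

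**Precision.** All three primary outcomes are measured at baseline. If baseline enters only by subtraction, the between-arm contrast carries more variance than it need, and a chance imbalance at baseline is only partly handled, because participants who start high tend to fall back and those who start low tend to rise. After the 20% dropout that the plan expects, 53 per arm leaves about 42, below the 44 that the plan calculates.

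**Interpretation.** A test of change within one arm does not use the randomised comparison. Participants in both arms may change for reasons unrelated to the intervention, such as repeated testing or being shown their results after each follow-up. A significant change in the intervention arm beside a non-significant one in control is easily read as an effect, and that pattern can arise when both arms change by the same amount.

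**Working it through.** **Inputs from the Sample size estimate section.** Two-sided α = 0.05; "80% power and an effect size of 0.6"; difference 750 steps; SD of change (5000 − 0)/4 = 1,250; dropout 20%. Allocation is 53 per arm (Blinding and randomization section). **Assumed, because the article gives no value:** r from 0.5 to 0.9, and equal variances at baseline and follow-up.

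**1. The plan's figure.** n = 2(1.96 + 0.84)² / (750/1250)² = 15.68/0.36 = 43.56, rounded up to 44 per arm. The article prints 43.60 and also rounds to 44, so its figure reproduces. After 20% loss, 53 × 0.8 = 42.4; I use 42 per arm.

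**2. Variance of the two analyses.** With a common SD s at each visit:
- change from baseline: 2s²(1 − r)
- follow-up adjusted for baseline: s²(1 − r²)
- ratio, adjusted to change: (1 + r)/2

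**3. Power for steps at 42 per arm.** The SD of change is held at 1,250, so the standardised effect becomes 0.6/√((1 + r)/2). Power is from the two-sample t-test.

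| Analysis | Variance ratio | Standardised effect | Power | CI narrower by |
|---|---|---|---|---|
| Change score | 1 | 0.600 | 77.6% | – |
| Adjusted, r = 0.5 | 0.75 | 0.693 | 88% | 13% |
| Adjusted, r = 0.6 | 0.80 | 0.671 | 86% | 11% |
| Adjusted, r = 0.7 | 0.85 | 0.651 | 84% | 8% |
| Adjusted, r = 0.8 | 0.90 | 0.632 | 82% | 5% |
| Adjusted, r = 0.9 | 0.95 | 0.616 | 80% | 2.5% |

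The normal approximation that the plan uses gives 78.5% for the first row, so the choice of method moves power by about one point.

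**4. Check by simulation.** In 4,000 simulated trials with 44 per arm and a true difference of 750, both estimators were unbiased. The standard error was 267 (change) against 231 (adjusted) at r = 0.5, and 263 against 246 at r = 0.7. The variance ratios of 0.75 and 0.87 agree with 0.75 and 0.85 from the formula.

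**5. Within-arm tests when the intervention adds nothing.** Suppose both arms truly change by the same amount, with 44 per arm and SD 1,250. The standard error of one arm's mean change is 1250/√44 = 188. If p is the chance that one arm is significant, the chance that exactly one of the two is significant is 2p(1 − p).

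| Common change (steps) | p | Exactly one arm significant |
|---|---|---|
| 0 | 0.050 | 9.5% |
| 200 | 0.186 | 30% |
| 375 | 0.512 | 50% |
| 530 | 0.803 | 32% |

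By symmetry, in half of these trials the significant arm is the intervention arm.

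**The case against.** The case on the other side is substantial on four points.

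- **Unadjusted analysis is not stated.** A reader might infer that the plan fixes an analysis of raw changes and excludes adjustment. The text does not say so. It uses the word raw only for the data behind the descriptive statistics, and naming the intervention as the independent variable need not be a full list of model terms. A mixed model with baseline among the responses and a common baseline mean would already gain about the same precision. Such detail may sit in an analysis plan that is not shown. This stands, and limits the point to what the text names: a comparison of changes with no baseline term.
- **The change analysis is not wrong.** It is unbiased under randomisation, and the sample size was built on the SD of change, so analysis and power calculation match. This stands. That 42 is below 44 comes from how the target was inflated for dropout, which is a separate matter.
- **Efficacy is not assigned to the within-arm tests.** A reader might infer that their p-values will decide whether the intervention works. The section gives the between-arm question to the mixed model and nowhere says this. What remains is that the tests are planned, judged at 0.05, and uninformative about the randomised comparison.
- **A completers-only analysis is not stated.** Classical repeated-measures ANOVA needs complete data, so one might infer that those tests drop anyone who misses a visit. The article gives no missing-data rule for them, so I do not rely on it.

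**Conclusion.** The point holds as an improvement in efficiency and reporting; there is no error that threatens validity. Baseline adjustment would cut the variance of the arm contrast in steps by 25% at r = 0.5 and 10% at r = 0.8, which raises power at 42 per arm from about 78% to about 88% or 82%. These figures rest on an assumed r, equal variances, and the plan's own rough SD of 1,250. They apply to steps only. For an outcome that tracks closely over time, as fat mass (%) may, r could be near 0.9 and the gain would be small. The within-arm part depends on no assumption about r: those tests are in the text, carry a significance threshold, and cannot show an intervention effect.

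**What to change.** For each primary outcome, fit one linear mixed model to all available week-13 and week-24 values, with baseline value, visit, arm and arm-by-visit as terms. Take the arm difference at each visit from that model, with its 95% confidence interval.

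Enter baseline as a covariate. Do not constrain the baseline means of the two arms to be equal. The Blinding and randomization section allocates participants after screening and makes them aware of their group, and the Testing schedule section places the baseline visits after enrolment. Baseline therefore appears to be measured after allocation, and equal means cannot be taken as guaranteed. Moving baseline before allocation would be a change of procedure and is not part of this fix.

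Replace the within-arm ANOVA sentence with within-arm mean changes and 95% confidence intervals, without p-values, and state that they are not evidence of an intervention effect.

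The cost is a few sentences of analysis text. No new data are needed, and the recruitment target need not change.
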